## Abstract

**Background:**

The health aspects, disease frequencies, and specific health interests of prisoners and refugees are poorly understood. Importantly, access to the health care system is limited for this vulnerable population. There has been no systematic investigation to understand the health issues of inmates in Switzerland. Furthermore, little is known on how recent migration flows in Europe may have affected the health conditions of inmates.

**Objective:**

The Swiss Prison Study (SWIPS) is a large-scale observational study with the aim of establishing a public health registry in northern-central Switzerland. The primary objective is to establish a central database to assess disease prevalence (ie, International Classification of Diseases-10 codes [German modification]) among prisoners. The secondary objectives include the following: (1) to compare the 2015 versus 2020 disease prevalence among inmates against a representative sample from the local resident population, (2) to assess longitudinal changes in disease prevalence from 2015 to 2020 by using cross-sectional medical records from all inmates at the Police Prison Zurich, Switzerland, and (3) to identify unrecognized health problems to prepare successful public health strategies.

**Methods:**

Demographic and health-related data such as age, sex, country of origin, duration of imprisonment, medication (including the drug name, brand, dosage, and release), and medical history (including the International Classification of Diseases-10 codes [German modification] for all diagnoses and external results that are part of the medical history in the prison) have been deposited in a central register over a span of 5 years (January 2015 to August 2020). The final cohort is expected to comprise approximately 50,000 to 60,000 prisoners from the Police Prison Zurich, Switzerland.

**Results:**

This study was approved on August 5, 2019 by the ethical committee of the Canton of Zurich with the registration code KEK-ZH No. 2019-01055 and funded in August 2020 by the “Walter and Gertrud Siegenthaler” foundation and the “Theodor and Ida Herzog-Egli” foundation. This study is registered with the International Standard Randomized Controlled Trial Number registry. Data collection started in August 2019 and results are expected to be published in 2021. Findings will be disseminated through scientific papers as well as presentations and public events.

**Conclusions:**

This study will construct a valuable database of information regarding the health of inmates and refugees in Swiss prisons and will act as groundwork for future interventions in this vulnerable population.

**Trial Registration:**

ISRCTN registry ISRCTN11714665; http://www.isrctn.com/ISRCTN11714665

**International Registered Report Identifier (IRRID):**

DERR1-10.2196/23973

## Introduction

### Background

In institutions such as prisons and correctional facilities, health risks are disproportionately widespread. The World Health Organization in the European Region has estimated that approximately 6 million people are incarcerated every year in this region [1]. The health profile of the people in prison is complex and the risk factors for poor health often overlap with the risk factors for incarceration [2]. Cooccurring physical and mental health conditions are often found in close association to entrenched and intergenerational social disadvantage [3]. Data indicate that, in general, prisoners are sicker when compared with counterparts of the same age, race, and sex in a free society [4]. Additionally, prisons and detention centers are known to reduce the resources for inmates substantially, and disease frequencies and the health of individual prisoners are poorly understood owing to the lack of original data [1]. Further, many inmates lack opportunities to articulate themselves (eg, language barriers in Europe), and access to the health care system is extremely limited. Prison physicians often speak of a “blind spot in society” [5]. In contrast to the investigations of the judicial branch, which is obliged to publish numbers on the origin, age, sex, and penalties of convicts, systematic investigations on the health issues of inmates are extremely rare.

### Current Situation

Only a few prevalence studies conducted in the United States and Europe indicate that the disease profile of prison inmates is significantly different from that of the general population. In line with what is generally known about the health of the people in prison, data from the Health in Prisons European Database paint a picture of an extremely vulnerable population that experiences poor health and engages in risky health behaviors, leading to noncommunicable and communicable diseases and mental health conditions [1,6]. In this setting, drugs and nonmedical use of conventional medications seem to play a crucial role in the health of the people in prison [6]. In 2014, a report from the European Monitoring Centre for Drugs and Drug Addiction (EMCDDA) suggested that besides health-related problems, illicit drug use is highly prevalent among people in prison [7]. More recently, the EMCDDA has warned about the rapidly developing phenomenon of the use of new psychoactive substances (NPS) among prisoners [8]. Monitoring data indicate that prisons are the epicenter of this phenomenon and there is growing concern that NPS may be responsible for a large share of drug-related problems in prison [8]. Approximately 4%-56% of all inmates use psychoactive substances, but the exact percentage requires further investigation [4,9]. For comparison, there is ample evidence that the “opioid crisis” in the United States affects inmates in particular [10]. Currently, only limited data from European institutions are available [8]. Studies conducted in the United States estimate that the “off-label” usage of drugs in prisons is about 36.2% [11]. However, no comparable data from Switzerland are available and there seems to be a lack of systematically collected and comparable data on the health of incarcerated people.

In 2017, approximately 71% of prison inmates in Switzerland were foreigners and most were imprisoned in the Canton of Zurich [12]. One way of systematically recording specific aspects of the disease burden in this population is to analyze medical files and histories. From studies performed in the early 2000s, it has been established that analysis of medical records in prisons is an extremely reliable source. In fact, in some areas of disease burden (eg, infectious disease, assessment of cardiovascular risk), this can be considered superior to information gained from questionnaires or personal interviews [9,13]. Most importantly, a systematic collection and analysis of medical records has not yet been conducted for inmates in Switzerland.

### Police Prison Zurich

Prison facilities are required to ensure adequate health care in both the somatic and psychiatric fields. The University Hospital Zurich has taken over the responsibility for providing somatic and psychiatric care to the Police Prison Zurich (PPZ) inmates. The PPZ is the largest inmate correctional facility in Switzerland, and approximately 10,000 to 12,000 prisoners are admitted per year. Data from the Federal Statistical Office in Switzerland indicate that inmates held for pretrial detention are predominantly young and male, and approximately 75% are non-Swiss nationals (Figure 1) [12]. Anecdotal evidence suggests that a large proportion of inmates (eg, refugees) have reported previously using drugs that were prescribed for off-label purposes. One example is the prevalent purchase of the substance *pregabalin* via web-based pharmacies [14]. Other examples include the underestimated usage of recreational drugs (eg, clonazepam) and other NPS [15]. Most of these drugs have potentially substantive health consequences, mainly attributed to their high potential for addiction and adverse effects. Furthermore, little information has been established on how recent refugee patterns may have affected the health conditions of the inmates in recent years.

**Figure 1 figure1:**
[figure not shown]
Imprisonment statistics for pretrial detention in Switzerland for year 2020 from the Federal Statistical Office.

### Hypothesis

In summary, the prison population is very vulnerable; yet, hardly any reliable data are available on the health of inmates [1,3]. The current geopolitical situation appears to exacerbate the problem as patients with a disproportionately poor health status have contact with the Swiss health care system. Data from the PPZ offer a unique opportunity globally for a representative analysis of the disease profile of inmates. The aim of this study is to collect health-related data in order to give insight into an unexplored area and underserved patient population. First, we hypothesize that the disease profile of inmates substantially differs from that of the general population. Specifically, certain chronic and psychiatric diseases are disproportionately prevalent among inmates and refugees. Second, a large number of drugs (eg, NPS) may be used “off-label,” and the origin of the inmates and the refugee route may have an impact on the disease profile of the affected. Third, recent geopolitical changes have significantly affected the overall disease profile of inmates.

## Methods

### Study Design

This is an observational study with a population-based cross-sectional baseline measurement and no prospective follow-up.

### Study Objectives

The primary objective is to establish a central database to assess the prevalence of diseases (ie, International Classification of Diseases [ICD]-10 codes [German modification]) among prisoners. The secondary objectives are (1) to compare the 2015 versus 2020 disease prevalence among inmates against a representative sample from the local resident population, (2) to assess longitudinal changes in disease prevalence from 2015 to 2020 by using cross-sectional medical records from all inmates at the PPZ, and (3) to identify unrecognized health problems to formulate models for successful public health strategies. Achieving these objectives can result in new insights into public health and in the construction of a valuable database of information regarding the health of inmates and refugees in Swiss prisons, thereby enabling future interventions in this vulnerable population.

### Study Questions

The main questions under investigation are as follows.

What is the health status of the inmate population and which conditions are overrepresented and underrepresented in the prison setting? In particular, how do psychiatric diseases affect inmates and what is the estimated prevalence of substance abuse in the prison population? Which infectious diseases (eg, tuberculosis, pneumonia, scabies) are highly prevalent among inmates and what are the comorbidities of this population?What are the dynamics in the health profile of inmates (and thus refugees) during the European migrant crisis from 2015 onwards and how does the epidemiology of the prison population affect the balance between acute and chronic conditions?Are there underrecognized health problems among vulnerable populations (eg, children, pregnant mothers, patients with suicidal ideation) or overrepresented populations (eg, body-packers, patients with traumatic injuries).

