### Participants

This study consists of prisoners within the PPZ from April 1, 2015 until August 31, 2020. The final sample will be exhaustive. All inmates within this timeframe will be included in this study and there will be no random selection. Only in documented cases wherein a prisoner allegedly refuses to participate in health-related activities, he or she will be excluded from the study and his or her data will not be analyzed. Otherwise, there are no exclusion criteria. Extrapolating from current numbers (approximately 850 prisoners per month × 64 months), it is expected that the final database will contain data from approximately 50,000 to 60,000 prisoners.

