### Statistical Considerations

Statistical analyses will be conducted by the study team in consultation with senior statisticians. For baseline analyses, means or medians will be reported according to the distribution of the continuous variable. Proportions will be reported for categorical variables. For hypothesis testing, a two-sided *t* test for normally distributed continuous variables and nonparametric tests for nonnormally distributed continuous variables will be conducted; chi-square testing will be used for categorical variables. Linear or logistic regression models with or without adjustment for potential confounders (ie, age, sex, nationality) will be used when appropriate. Regression analysis estimates will be reported using 95% confidence intervals, and a two-sided *P* value of <.05 will be considered statistically significant for all reported tests. For the longitudinal data, a generalized linear mixed model with random effects (accounting for the nationality of the prisoner during the refugee crisis) will be used when appropriate. Statistical analyses will be performed using STATA Version 16 (StataCorp LP).

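### Hypothesis 3 attributes change in disease profile to geopolitical events, but the records have no pre-crisis baseline and the stated model has no contrast that separates migration from other change over calendar time

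*Protocol article*

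**What the plan says.** The Hypothesis section of the protocol article says: "Third, recent geopolitical changes have significantly affected the overall disease profile of inmates". The sentences before it suggest a route: people in disproportionately poor health come into contact with the Swiss system.

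Study Questions places the exposure in time as "during the European migrant crisis from 2015 onwards", with no end date. Participants states "This study consists of prisoners within the PPZ from April 1, 2015 until August 31, 2020". The Abstract gives an earlier first month; there the data "have been deposited in a central register over a span of 5 years (January 2015 to August 2020". Study Design describes a "population-based cross-sectional baseline measurement and no prospective follow-up".

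For the time trend, Statistical Considerations offers "a generalized linear mixed model with random effects (accounting for the nationality of the prisoner during the refugee crisis", to be used when appropriate. It lists age, sex and nationality as potential confounders for the other regressions.

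A comparison group is planned. Study Objectives and Outcomes set inmates against a sample of local residents, and Cooperation says that an insurer will supply a matched Swiss cohort drawn from its drug report. Table 1 records country of origin and date of imprisonment for inmates.

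**The concern.** The third hypothesis names a cause. To support it, the data must show either that the profile changed when the exposure began, or that it changed differently in groups more and less exposed. The first is impossible inside this window. The second is possible with the variables collected, but the article does not state it as an analysis.

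What remains is a change over calendar time in all inmates. Documentation habits, coding and police practice also change over calendar time. The article's own dates make a recording difference plausible. Data collection began in August 2019 (Results), so 2015 records can only have been abstracted retrospectively, whereas Data Collection and Management allows synchronous entry, which was feasible for 2020.

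How nationality enters the model also matters. If migration acts mainly by changing who is admitted, conditioning on nationality tends to absorb that route. It leaves the within-nationality trend, which is where recording artefacts also sit.

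The Discussion says that findings will go to policymakers, so an unsupported attribution to migration would have consequences.

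**Working it through.** **Size of the database.** Participants multiplies 850 per month by 64 months: 850 × 64 = 54,400, inside the stated 50,000 to 60,000. April 2015 to August 2020 is 65 calendar months (55,250), and January 2015 to August 2020 is 68 (57,800). Both are also inside the range.

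**Baseline.** Months before 2015: zero under either start date.

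**End-year samples.** At 850 per month, April-December 2015 gives 850 × 9 = 7,650 and January-August 2020 gives 850 × 8 = 6,800.

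**Effect of recording drift common to all inmates.** Assume that recorded prevalence rises from 10% to 12% with no true change.
- SE of the difference = √(0.10 × 0.90/7,650 + 0.12 × 0.88/6,800) = 0.0052.
- z = 0.02/0.00522 = 3.83, P = .0001.
- Chance of two-sided P<.05: about 97%.

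Other cases, same method (the prevalences are assumptions):

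| Recorded prevalence | All inmates | One third of inmates |
|---|---|---|
| 10% to 12% | 97% | 60% |
| 5% to 6% | 75% | 33% |
| 10% to 10.5% | 17% | 8% |

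The last column uses the statement in Study Site that about a third need medical care: 2,550 against about 2,267.

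**What an internal comparison would cost.** Police Prison Zurich puts non-Swiss nationals at about 75%. That is a national pretrial-detention figure, and it is assumed here to apply to this prison. With the same 10% and 12%:
- Swiss, n = 1,912.5 and 1,700: SE of change = 0.0104.
- Non-Swiss, n = 5,737.5 and 5,100: SE of change = 0.0060.
- SE of the difference in changes = √(0.0104² + 0.0060²) = 0.0121, so the 95% half-width is 1.96 × 0.0121 = 2.4 percentage points.
- Ratio to the crude contrast: 0.0121/0.0052 = 2.3. A real 2-point difference in change would be detected about 38% of the time from the end years alone.

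**Why the interaction cannot stand alone.** Let w be the non-Swiss share, and p_S and p_N the Swiss and non-Swiss prevalences. Overall prevalence is p_S + w(p_N − p_S). If only w changes, the overall change is Δw(p_N − p_S), while the interaction is zero. A change that acts through the mix would be missed.

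**Why it is not a perfect control.** Suppose recording rises from 80% to 90% of cases, with assumed true prevalences of 10% (Swiss) and 20% (others). Recorded prevalence goes from 8% to 9% and from 16% to 18%. The false difference in change is 2 − 1 = 1 point on the absolute scale. On a ratio scale it is zero, because both rise by a factor of 1.125.

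**The case against.** The strongest reply has four parts.

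*The plan is mostly descriptive.* Asking about dynamics during the crisis needs no earlier period, and the trend objective and outcome speak only of longitudinal change. That stands: Study Questions is not at fault. The problem is the causal sentence in the Hypothesis section, read with the model in Statistical Considerations.

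*There is a comparison group.* A reader might infer that the study has none. The article contradicts this, because a resident cohort is planned for 2015 versus 2020. But that cohort is not linked to hypothesis 3, and it comes from a different recording system, so it does not cancel drift in prison records.

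*Drift is partly controlled and need not matter.* One physician team uses one case report form, and Quality Control adds a two-reader check on 150 patients. This limits coding drift. It does not test whether source diagnoses were documented alike across the years, and the only check with a monthly axis concerns medication. A reader might also infer that any drift, however small, would come out significant. The table shows otherwise: 10% to 10.5% reaches P<.05 only 17% of the time.

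*Model detail belongs in an analysis plan.* The article does not say that the random effects are intercepts only, so random time slopes by nationality are not excluded. That is fair, and an unseen plan may specify a contrast. It could not create a pre-2015 baseline in this window, and the causal wording is fixed here.

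It is also right that Swiss inmates are an imperfect control. Language barriers and foreign documents could make recording drift differ by origin.

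**Conclusion.** The point holds for the causal reading of hypothesis 3 and no further. No data precede the crisis as the article dates it, and neither the resident cohort nor the random effects for nationality are set up as a contrast that separates migration from other calendar-time change. A significant 2015-2020 difference would therefore show change during the period, not its cause.

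The risk comes from moderate drift. An assumed common rise in recording from 10% to 12% would be significant about 97% of the time with all inmates as denominator, and about 60% with a third of them. These figures rest on 850 admissions per month, a comparison of the two end years, and prevalences that the article does not give. Describing prevalence over 2015-2020 remains sound.

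**What to change.** Keep the data window.

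1. Word hypothesis 3 and its conclusion as change in the inmates' disease profile during 2015-2020, not as an effect of geopolitical events.
2. Report the crude 2015-2020 change split into the part due to changed origin mix and the part within origin groups. With group shares w and prevalences p: overall change = Σ Δw × mean p + Σ mean w × Δp, where each mean is over the two years.
3. Add an origin-group-by-calendar-time interaction, with Swiss inmates as the concurrent comparator and the origin groups fixed before analysis. Report it as a supporting check, not as the sole test, and state the scale.

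The variables needed are already in Table 1, so the change affects wording and analysis only. The price is precision: the interaction's standard error is about 2.3 times that of the crude contrast if the national 25/75 split applies. It also removes only artefacts that Swiss and non-Swiss inmates share on the chosen scale, and the report should say so.

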### Study Site

The health registry is based at the PPZ ([name]). In this prison, all inmates of the Canton of Zurich are detained for up to a maximum of 7 days. Thereafter, prisoners are transferred to any of the following systems: (1) pretrial detention, (2) serving a particular prison sentence in a long-term facility, (3) anticipatory execution of sentence, or (4) subjection to coercive measures based on Aliens Act. The PPZ is the only central police prison in the Canton of Zurich serving a population of 1,520,968 (as of December 31, 2018), which is the most populous canton in the country. This prison has approximately 10,000 to 12,000 inmates yearly, of which about a third require medical attention (based on historical data from the PPZ/not published). The entire spectrum of medical attention needed to meet inmates’ medical needs is covered within the PPZ, such as general internal medicine (eg, asthma), traumatic injuries, psychiatric emergencies, and infectious diseases (eg, HIV).

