### Outcomes

The primary outcome measure will be disease prevalence by using cross-sectional data from prisoner’s medical records (ie, using the ICD-10 codes [German modification]) from 2015 to 2020. Secondary outcome measures include the following: (1) A comparison of disease prevalence (ICD-10 codes [German modification]) of the inmates at the PPZ to that of a representative sample from the local resident population by using cross-sectional medical records from all inmates at the PPZ from 2015 to 2020 and (2) longitudinal changes in disease prevalence (ICD-10 codes [German modification]) from 2015 to 2020 by using cross-sectional medical records from all inmates at the PPZ.

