## Discussion

This health registry is designed to provide new public health insights into a group of vulnerable patients. The implementation of the study protocol promises to allow for the identification of specific health problems to help prepare successful public health strategies to meet these challenges. To gain a representative sample from the Canton of Zurich inmate population, this study required a high enrollment. Inmates at the PPZ usually spend a minimum of 1 day to a maximum of 7 days in the facility; they are internationally mobile, often unable to speak German, and have no contact details provided. Gaining informed consent from each prisoner is a disproportionately large expenditure. In this observational study, we assume that the expected increase in knowledge will benefit future inmates and thus, outweigh the disadvantages associated with privacy concerns. Moreover, given these operational challenges, any large-scale study on the prisoner population will likely need to be conducted without receiving individualized informed written consent. Thus, in accordance with the Swiss Human Research Act Article 34, the need to obtain informed consent is waived for this study, and data collected from all prisoners will be gathered. Only in case of documented alleged refusal to participate in health-related activities, data from the prisoner will not be included in this study.

Currently, no similar observational studies on Swiss inmates are available. Data from the United States and European registries indicate that prisoners are sicker when compared with their counterparts in a free society [2-4]. However, these data are limited to a certain location and time and they do not investigate changes over time within a certain cohort. Preliminary studies suggest that illicit drugs and especially NPS are a growing problem in European prisons, but only limited data from European prisons are available [7,8]. This study will be able to draw conclusions on these issues based on a 5-year representative sample of approximately 50,000 to 60,000 prisoners from the PPZ. Thus, this study will add valid evidence to the current health status of prisoners, and findings can be used to promote healthy behaviors (eg, future intervention studies) or policy change for this population.

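### All inmates form the study base, but diagnoses come from medical records when only about a third need medical attention, so the primary prevalence has no settled denominator and may be understated

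*Protocol article*

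**What the plan says.** **Study base.** The Participants section of the protocol article calls the sample exhaustive: "All inmates within this timeframe will be included in this study and there will be no random selection". Documented refusal is the only ground for leaving someone out: "Otherwise, there are no exclusion criteria". The expected size is extrapolated from "approximately 850 prisoners per month × 64 months" and given as roughly 50,000 to 60,000. The Discussion calls a sample of that size representative.

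**Source of the outcome.** The Outcomes section states: "The primary outcome measure will be disease prevalence by using cross-sectional data from prisoner’s medical records". The secondary comparison with residents is to be made "by using cross-sectional medical records from all inmates at the PPZ from 2015 to 2020". Under Data Collection and Management, physicians enter the data from source documents held in the prisoner's medical history.

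**Access to a diagnosis.** The Study Site section says: "This prison has approximately 10,000 to 12,000 inmates yearly, of which about a third require medical attention". It labels this as unpublished historical data. The Discussion adds: "Inmates at the PPZ usually spend a minimum of 1 day to a maximum of 7 days in the facility". In Table 2 the initial physician assessment is a yes/no item recording whether it was needed. No examination of every inmate is described.

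**The concern.** These statements do not fit together. A medical record can supply a diagnosis only for someone whose health was looked at, and the article's own figure suggests that this is a minority of the people it counts. For an inmate without a medical contact, the absence of a code means that the disease was not looked for. It does not mean that the disease was absent.

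The article leaves two bases open, and neither gives disease prevalence among all inmates:

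- **All inmates as denominator.** The result is closer to a rate of medical presentation in custody. It is lowest relative to the truth for chronic or silent conditions that need not surface within 7 days.
- **Only inmates with records as denominator.** The group is selected for needing care, and the terms exhaustive and representative no longer apply.

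Both secondary outcomes inherit the problem. The resident figures come from health-insurer data (Cooperation section), which do not arise from a custody window of a few days. The 2015 to 2020 trend would also move with any change in the share of inmates seen, even if disease did not change.

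**Working it through.** **The plan's own figure.** 850 × 64 = 54,400, which lies within the stated 50,000 to 60,000. April 2015 to August 2020 inclusive is 65 months, and 850 × 65 = 55,250. The difference of 1.6% does not matter here.

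**Inputs.**
- f, the share of inmates seen: 1/3, from the Study Site section. That section speaks of requiring attention; equating this with having a medical contact is an assumption.
- r, the prevalence among unseen inmates divided by that among seen inmates: not given in the documents. It is an assumption, shown from 0 to 2.
- p, the prevalence among seen inmates: 10%, for illustration only.

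**Inmates with and without a contact.** 54,400 / 3 ≈ 18,133 seen, and 54,400 − 18,133 = 36,267 unseen. Over the stated range the seen group is 50,000 / 3 ≈ 16,700 to 60,000 / 3 = 20,000.

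**Base 1: all inmates, with a missing code read as no disease.**
- Recorded prevalence = f × p
- True prevalence = f × p + (1 − f) × r × p
- Understatement factor = true / recorded = 1 + r(1 − f)/f

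With f = 1/3, (1 − f)/f = 2 and the factor is 1 + 2r. At p = 10% the recorded figure is always 10% / 3 = 3.3%.

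| r | true prevalence | factor |
|---|---|---|
| 0 | 3.3% | 1 |
| 0.5 | 6.7% | 2 |
| 1 | 10.0% | 3 |
| 2 | 16.7% | 5 |

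At r = 1 the factor is 1/f. For f = 0.40 it is 2.5, and for f = 0.25 it is 4.0.

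**Base 2: only inmates with records.** The reported figure is p, and reported / true = 1 / (f + (1 − f)r). With f = 1/3 this is 3 at r = 0, 1.5 at r = 0.5, 1 at r = 1 and 0.6 at r = 2. This base therefore overstates prevalence when unseen inmates are healthier and understates it when they are sicker.

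**Trend on base 1.** With p constant, recorded prevalence is proportional to f, so the ratio between two years is f₂/f₁. The documents give no yearly shares. By assumption, starting from 30%, a move to 27% gives 27/30 = 0.90, to 33% gives 33/30 = 1.10, and to 36% gives 36/30 = 1.20. The last would be an apparent 20% rise with no change in disease among those seen.

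**The case against.** The strongest reply is that the article never says codes exist only for the third needing attention, and never says unseen inmates are to be scored negative. It names medical records from all inmates as the base for the secondary outcomes. It says incomplete data will be made visible in the registry. It takes some health items in Table 2, such as illicit drug history, opioid replacement and benzodiazepine dependence, from the police, so these need not depend on a consultation. A condensed article may also leave missing-data rules to a fuller document.

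Most of this stands as a limit on the claim. A reader might infer that the plan scores unseen inmates as disease-free and that a threefold understatement is established. The documents support neither. Nor is threefold a ceiling: it needs r = 1 and f = 1/3, it falls to no understatement at r = 0, and it is exceeded if a condition is commoner among the unseen. The one-third share is itself unpublished.

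It is also fair that a downward bias is conservative for the hypothesis that certain diseases are more frequent among inmates. An excess found on the full denominator would survive this particular bias.

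The reply does not remove the conflict. The study base, the source of the outcome and the one-third figure are all stated in the article, so this is more than an omitted detail. The remark on incomplete data sets no rule for inmates who were never seen. The police-sourced items are not the primary outcome, which rests on ICD-10 codes in medical records.

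**Conclusion.** The concern holds in conditional form. As described, the plan does not deliver disease prevalence in all inmates. It delivers either recorded presentation over the full intake or prevalence in a subgroup of about 16,700 to 20,000 selected for needing care. For the same recorded cases the two figures differ by 1/f, which is threefold at f = 1/3.

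If the full intake is used and a missing code is read as no disease, the understatement at f = 1/3 runs from none (r = 0) to fivefold (r = 2), and is threefold if unseen inmates are as ill as seen ones. This rests on three assumptions: that diagnoses depend on a medical contact, that about a third have one, and a value of r that the documents do not supply.

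The resident comparison and the trend share the weakness. A false trend is a possibility; nothing in the documents shows that the share seen changed. Because the primary outcome and both secondary outcomes are affected and the remedy is cheap, it should be settled before analysis.

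**What to change.** 1. Derive a medically assessed yes/no flag for every admission from data already held. The Table 2 item on the reason for seeing a physician is one likely source.
2. State that the absence of a medical record is not treated as the absence of disease, in the tables or in the regressions.
3. Report recorded prevalence by year on two denominators. All admissions gives a lower bound. Medically assessed inmates gives an upper figure only if unseen inmates are no sicker than seen ones, and that condition should be printed beside it.
4. Report the share assessed by year, age, sex and country of origin.
5. Present the trend and the resident comparison on both denominators as a sensitivity check. Neither alone is safe: the full denominator moves with the share seen, and the assessed-only one moves with case mix if the threshold for a consultation changes.
6. Describe the target as recorded disease during short-stay police detention, and restrict the word representative accordingly.

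The cost is analysis-plan wording and one derived variable, with no new data collection. The headline becomes a range, and the sample carrying diagnostic information is stated as about 18,000 instead of 50,000 to 60,000.
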